#### **4.2.7. Inclusion Criteria (Prodromal Subjects)**

- 4.2.7.1. Subjects must have at least one of the following characteristics:
  - Hyposmia:*
    - a) Male or female age 60 years or older
    - b) Confirmation from olfactory core that olfaction as determined by UPSIT is at or below the 10th percentile by age and gender
  - REM Behavior Disorder (RBD):*

- a) Male or female age 60 years or older
  - b) Confirmation from sleep core that subject's Polysomnography (PSG) meets criteria for RBD and/or clinical diagnosis of RBD by site investigator including existing PSG.
- 4.2.7.2. Confirmation from imaging core that screening dopamine transporter SPECT scan (or V-MAT-2 PET scan for sites where DaTSCAN™ is not available) is read as eligible (see below)
- About 80 subjects will have a range of DAT deficit similar to subjects with early PD (mild to moderate DAT deficit). About 20 subjects will be selected with no DAT deficit or minimal DAT deficit similar in age, gender, and risk profile to those with mild to moderate DAT deficit.
- 4.2.7.3. Ability to provide written informed consent in accordance with Good Clinical Practice (GCP), International Conference on Harmonization (ICH), and local regulations.
- 4.2.7.4. Willing and able to comply with scheduled visits, required study procedures and laboratory tests.
- 4.2.7.5. Women may not be pregnant, lactating or planning pregnancy during the course of the study.
- Includes a negative urine pregnancy test on day of screening scan prior to injection (DaTSCAN™).
  - Includes a negative serum pregnancy test prior to Screening scan injection (F-AV-133 only).
- 4.2.7.6. Women participating in VMAT-2 PET imaging must be of non-childbearing potential **or** be using a highly effective method of birth control 14 days prior to until at least 24 hours after injection of F-AV-133).
- Non-child bearing potential is defined as a female that must be either postmenopausal (no menses for at least 12 months prior to Screening) or surgically sterile (bilateral tubal ligation, bilateral oophorectomy or hysterectomy).

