- 14.4.3. **Examination of whether short-term change in progression endpoints is predictive of change in long-term endpoints.** The third set of analyses will examine whether short-term changes in the progression endpoints are predictive of changes in long-term endpoints in the MDS-UPDRS score. This analysis will examine a subset of the progression endpoints. Only progression endpoints that show differences between subsets will be considered (since for example, a marker that doesn't distinguish PD patients from healthy subjects would not be thought to be a biomarker for long-term outcome in PD patients). All progression endpoints that meet these criteria will be modeled using a process similar to that described above. The primary focus will be on the long-term change in the UPDRS score. However, additional long-term endpoints may be considered as well. Because this modeling process involves longer term endpoints, which would be much harder to replicate, a ten-fold cross validation procedure will be used to test the predictive validity of each model. If successful, the final model will provide a subset of one or more short-term progression endpoints that are predictive of the change in one or more of the long-term endpoints. This would suggest that these short-term progression endpoints are valid biomarkers for future studies of interventions in PD patient populations.
- 14.4.4. **Examination of PD Subsets.** Each of the first three sets of analyses will be repeated comparing subsets of PD subjects, rather than PD subjects vs. healthy subjects. If successful, the final model from these subset comparisons will determine whether some of the short-term progression endpoints are more predictive of long-term change in the MDS-UPDRS score for some subsets of PD subjects and less predictive for other subsets of PD subjects.
- 14.4.5. **Calculation of the proportion of SWEDD subjects that have a change in diagnosis over the 24-month evaluation period.** The analysis will involve identifying all SWEDD subjects that have a change in diagnosis from PD to another diagnosis. The percentage and 95% confidence interval will be reported. The other possible diagnoses will be further divided into 2 categories: 1) Other parkinsonian syndrome with a dopamine transporter deficit; 2) Other condition without a dopamine transporter deficit. The same information will be reported as well by these two categories.

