- 14.4.6. **Exploratory analysis of Prodromal subjects that phenoconvert.** The analysis will involve estimating the percentage of Prodromal subjects that

phenoconvert to PD within 2 years. The percentage and 95% confidence interval will be reported.

**14.4.7. Exploratory analyses of biomarkers for predicting phenoconversion among Prodromal Subjects.** This set of analyses will examine whether short-term changes in the progression endpoints are predictive of phenoconversion among Prodromal subjects. All progression endpoints will be considered. The examination will involve fitting a logistic regression model for phenoconversion, with each progression endpoint serving as a covariate.

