| 300               | 0.16                   | 17%                                 | 0.33                                          |
| 400               | 0.14                   | 14%                                 | 0.28                                          |
| 450               | 0.14                   | 15%                                 | 0.28                                          |
| 600               | 0.11                   | 13%                                 | 0.24                                          |

The planned sample size of approximately 80 SWEDD subjects is based on the estimated percentage of SWEDD subjects that will be observed over the recruitment period for the PPMI study. This is based on preliminary data from the study suggesting that about 20% of subjects screened with parkinsonian symptoms have no evidence for dopamine transporter deficit. The clinical and biomarker data from the SWEDD subjects will serve as a disease control population and will allow for a number of important exploratory assessments comparing the SWEDD subjects to the PPMI PD subjects and Healthy Controls.

The planned sample size of approximately 100 for the prodromal cohort is based primarily on prior exploratory studies. Nevertheless, based on preliminary data from studies combining olfactory loss, RBD, or LRRK2 mutation with DAT imaging deficit to define an at-risk population, we estimate 30% phenoconversion during the 24 month evaluation post DAT imaging. Under this assumption, the sample size will allow estimating the phenoconversion rate with a 95% confidence interval width of approximately  $\pm 10\%$ . It is further anticipated that the change in clinical, imaging, and biomarker data from the Prodromal cohort will allow for a number of important exploratory assessments comparing Prodromal subjects who convert to Prodromal subjects who do not convert. Finally, additional exploratory assessments will compare the Prodromal subjects to the PPMI PD subjects, Healthy Controls, and SWEDD subjects.

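### Section 14.4.7 sets an all-endpoint logistic model for phenoconversion on about 30 expected events, without the endpoint screen or ten-fold cross-validation that 14.4.3 uses for the parallel question

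*Protocol*

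**What the plan says.** Section 14.4.7 of the protocol, labelled exploratory, asks whether early changes in the markers predict phenoconversion among Prodromal subjects. It fixes the candidate set, "All progression endpoints will be considered", and the method: "The examination will involve fitting a logistic regression model for phenoconversion, with each progression endpoint serving as a covariate". It gives no list or count of endpoints, no screening or selection step, no shrinkage, no multiplicity rule and no validation. It names no time horizon either; the neighbouring 14.4.6 counts subjects who "phenoconvert to PD within 2 years".

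The size of the cohort and the event rate come from 14.5: "The planned sample size of approximately 100 for the prodromal cohort is based primarily on prior exploratory studies", and "we estimate 30% phenoconversion during the 24 month evaluation post DAT imaging". Section 4.2.7 adds: "About 80 subjects will have a range of DAT deficit similar to subjects with early PD"; about 20 more are to have minimal or no deficit.

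Section 14.4.3 treats the parallel question, whether early change predicts long-term MDS-UPDRS change. It lets in only endpoints that already differ between subsets, and then "a ten-fold cross validation procedure will be used to test the predictive validity of each model". Its stated reason is that longer-term endpoints are hard to replicate.

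The opening of 14.4 defers further analysis detail to a Data Analysis Plan, which is not at hand.

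**The concern.** The two prediction analyses are handled unevenly, and the safeguards sit on the wrong one. The PD analysis has 300 to 400 PD subjects by the figures in 14.5, a screened endpoint list and cross-validation. The prodromal analysis has about 100 subjects, about 30 events and an unscreened list, and no validation is stated. The reason 14.4.3 gives for cross-validating applies at least as well to conversion over two years in a cohort that, by section 4.1, takes about 400 screening scans to assemble.

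The sentence on the model can also be read two ways. As one joint model, it has few events per covariate, and its in-sample discrimination is biased upwards. As one model per endpoint, overfitting is not the issue, but many tests are run with no error control stated. In either case, the result could send follow-up work after markers that are indistinguishable from chance.

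**Working it through.** **1. The plan's own figure.** Section 14.5 says "the sample size will allow estimating the phenoconversion rate with a 95% confidence interval width of approximately" ±10%. With n = 100 and p = 0.30, the Wald half-width is 1.96 × √(0.30 × 0.70 / 100) = 0.090. The Wilson half-width is 0.088, and the Clopper-Pearson interval is 21.2% to 40.0%. The stated precision is reproduced, so the 100 subjects and 30% can be used as inputs.

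**2. Expected events.**
- 100 × 0.30 = 30.
- The 30% is drawn from studies of at-risk groups with a DAT deficit. Applied only to the 80 such subjects, it gives 80 × 0.30 = 24.
- With a 25% loss, a figure 14.5 states for the PD sample and borrowed here only as a sensitivity value: 75 × 0.30 = 22.5.

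**3. Number of endpoints, k (assumed).** Section 14.4.2 ties short-term change to the first six months. At Month 6 the Prodromal schedule repeats nine clinical instruments (MDS-UPDRS, Schwab & England, Epworth, the REM sleep questionnaire, GDS-15, STAI, QUIP, SCOPA-AUT and cognitive categorization) plus blood, urine and CSF: roughly 10 to 12 before sub-scores or analytes are counted. Month 12 brings this to about 20 with MoCA, five neuropsychological tests, PASE, DAT imaging and, at selected sites, DTI. The range k = 10 to 20 is therefore used, with 25 as an upper case.

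**4. Joint model on pure noise.** Simulation with n = 100, exactly 30 events, k independent normal covariates unrelated to outcome, and 400 runs per k. Events per covariate = 30 / k. The cross-validated column uses stratified ten-fold cross-validation.

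| k | Events per covariate | Mean apparent AUC | Apparent AUC ≥ 0.70 | Any covariate p<0.05 | Overall LR test rejects | Cross-validated AUC |
|---|---|---|---|---|---|---|
| 10 | 3.0 | 0.70 | 47% | 45% | 10% | 0.51 |
| 15 | 2.0 | 0.74 | 80% | 57% | 10% | 0.50 |
| 20 | 1.5 | 0.78 | 98.5% | 73% | 12% | 0.50 |
| 25 | 1.2 | 0.82 | 99.8% | 83% | 19% | 0.50 |

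The AUC in new subjects is 0.50 by construction, and cross-validation recovers it.

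**5. Sensitivity of the apparent AUC (k = 10 and k = 20, 300 runs each).**
- Pairwise covariate correlation 0.3: 0.70 and 0.78.
- 24 events in 100: 0.71 and 0.80.
- 22 events in 75: 0.73 and 0.83.
- 120 events in 400, if the 300 unaffected genetic subjects were added at the same assumed 30% rate: 0.60 and 0.64.

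**6. One model per endpoint.** For independent noise markers tested at 0.05 (the level stated in 14.4.1, assumed to carry over), the chance of at least one false positive is 1 − 0.95^k: 1 − 0.95^10 = 40%, 1 − 0.95^20 = 64%, 1 − 0.95^25 = 72%. The expected number of false positives is 0.05 × k: 0.5, 1.0 and 1.25. Correlation between markers would change these figures.

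**The case against.** The best defence has four parts.

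- **Exploratory and summary-level.** Section 14.4.7 is labelled exploratory, 14.5 presents the study as a screen for candidates to follow up, and 14.4 leaves detail to the Data Analysis Plan. Penalisation and validation may well appear there. This stands as far as it goes: what 14.4.7 omits, it does not exclude. But it does commit to a candidate set and a model, and the protocol states a safeguard for one prediction analysis and not for its weaker sibling.
- **One model per endpoint.** The wording allows this, and the AUC figures then do not apply. That also stands. It replaces overfitting with unadjusted multiple testing, and the ambiguity itself needs settling.
- **The event count is not fixed.** Section 14.4.7 names no horizon, section 4.1 follows the cohort for 5 to 10 years, and 14.1 can be read as including the Unaffected Genetic Cohort. More events would ease the problem, but the only conversion rate given is for the prodromal cohort at 24 months.
- **14.4.3 claims more.** Success there would suggest valid biomarkers, and 14.4.7 makes no such claim. This lowers the stakes; an in-sample AUC remains a poor guide to what deserves follow-up.

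A reader might infer that the model is bound to look predictive even if every marker is noise. The documents do not support that. The endpoint count is unknown, and AUC is not named as the measure. At 10 endpoints, noise reaches an AUC of 0.70 in only about half of runs, and the overall likelihood-ratio test rejects in only 10% to 19% of runs for 10 to 25 endpoints. Nor do the documents say that the model is unpenalised or that validation is ruled out.

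**Conclusion.** The point holds as a gap between two parallel analyses. Section 14.4.7 sets an all-endpoint logistic model on about 30 expected events (about 24 on the narrower reading) without the endpoint screen and cross-validation of 14.4.3. In a joint model, noise alone gives a mean apparent AUC of about 0.70 to 0.78 for 10 to 20 endpoints, and about 0.82 at 25, against 0.50 in new subjects. Fitted singly, the chance of at least one false lead is about 40% to 64% for 10 to 20 independent markers.

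These sizes rest on an assumed endpoint count, the 100-subject cohort, a 24-month horizon and the 30% rate. The 25-endpoint figures are an upper case, because short-term change is tied to six months. The analysis is exploratory, so the matter is one of interpretable reporting and does not touch the primary objective. It is worth changing because a better method is already in the protocol and costs little.

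**What to change.** In 14.4.7, state whether the model is joint or one per endpoint, and over what horizon conversion is counted.

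- **If joint:** use penalised logistic regression. Apply the ten-fold cross-validation of 14.4.3, with any selection or tuning repeated inside each fold. Stratify the folds on conversion, since 30 events over ten folds leaves about three per fold. Report the cross-validated discrimination as the result, not the in-sample value.
- **If per endpoint:** list the endpoints tested and report them with false-discovery-rate control.

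Both routes keep the stated intent to consider all endpoints. A cap of about three covariates (30 events at ten per covariate) would not, and is not needed once the model is penalised and cross-validated.

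The cost is a few sentences and computing time, with no change to data collection or sample size. The downside is that reported discrimination will be less favourable and fewer single markers may be flagged.

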#### **14.5. Determination of Sample Size**

As summarized above, much of the proposed analysis plan for the PPMI study is focused on a set of exploratory analyses with the goal of identifying short-term progression markers that can be used as biomarkers for future studies in PD patient population. Because of the exploratory nature of these analyses, it is very difficult to provide a formal sample size justification for the entire model building process. Furthermore, the PPMI study has a broad range of goals that reach beyond any single, pre-planned analysis. However, we can examine the ability of the proposed sample size to detect meaningful effects of interest for the preliminary comparisons of baseline characteristics and univariate assessments of progression markers across the groups of interest.

The table below provides generic information about the detectable effect sizes for three types of statistical analysis that may be performed on the PPMI data. For each analysis the two-sided alpha level is set to 0.05 and the beta level to 0.80. The first column gives the total sample size assumed to be available for the analysis, in the first two rows either 400 (total PD sample) or 300 (PD sample after allowance for 25% withdrawals). The third and fourth rows of the table correspond to the total sample size of 600 (400 PD, 200 HC) when, respectively 75% and 100% of the subjects are available for analysis. The second column gives the detectable correlation coefficient between two continuous measures (e.g., change in striatal  $\beta$ -CIT uptake vs. change in total MDS-UPDRS). The third column gives the detectable difference in prevalence rates of some characteristic (e.g. presence of dopaminergic side effects) between two “halves” of the sample (e.g. the younger patients vs. the older patients, with age dichotomized at the median for the entire group). For the first two rows the third column gives the detectable “effect size”, expressed as ratio of difference in means to standard deviation, for comparing two “halves” of the sample (e.g. younger vs. older patients as above) in relation to a continuous measure (e.g. change in total MDS-UPDRS). For the third and fourth row the comparisons are between PD patients and HC. The table suggests that the PPMI trial is adequately powered to detect effects that would generally be of clinical interest. While possible that smaller effects than those listed in the table might also be of clinical interest, it was determined that the added power for these comparisons did not offset any additional costs and logistical issues that would accompany a larger study in this population. Rather, the proposed study should prove to be effective for screening a large number of variables and identifying those that show the most promise for further exploration in follow-up studies.

| Total sample size | Detectable Correlation | Detectable Difference in Prevalence | Detectable Difference in Means (Standardized) |
|--------------------------|-------------------------------|--------------------------------------------|------------------------------------------------------|
| 300               | 0.16                   | 17%                                 | 0.33                                          |
| 400               | 0.14                   | 14%                                 | 0.28                                          |
| 450               | 0.14                   | 15%                                 | 0.28                                          |
| 600               | 0.11                   | 13%                                 | 0.24                                          |

The planned sample size of approximately 80 SWEDD subjects is based on the estimated percentage of SWEDD subjects that will be observed over the recruitment period for the PPMI study. This is based on preliminary data from the study suggesting that about 20% of subjects screened with parkinsonian symptoms have no evidence for dopamine transporter deficit. The clinical and biomarker data from the SWEDD subjects will serve as a disease control population and will allow for a number of important exploratory assessments comparing the SWEDD subjects to the PPMI PD subjects and Healthy Controls.

The planned sample size of approximately 100 for the prodromal cohort is based primarily on prior exploratory studies. Nevertheless, based on preliminary data from studies combining olfactory loss, RBD, or LRRK2 mutation with DAT imaging deficit to define an at-risk population, we estimate 30% phenoconversion during the 24 month evaluation post DAT imaging. Under this assumption, the sample size will allow estimating the phenoconversion rate with a 95% confidence interval width of approximately  $\pm 10\%$ . It is further anticipated that the change in clinical, imaging, and biomarker data from the Prodromal cohort will allow for a number of important exploratory assessments comparing Prodromal subjects who convert to Prodromal subjects who do not convert. Finally, additional exploratory assessments will compare the Prodromal subjects to the PPMI PD subjects, Healthy Controls, and SWEDD subjects.

The planned sample size of 600 subjects with either a LRRK2, GBA or SNCA mutation is based primarily on exploratory studies and considerations regarding the availability of subjects with PD and family members with these genetic mutations. The clinical and biomarker data from the Genetic Cohort will allow for a number of important exploratory assessments comparing the genetic PD and early PD subjects and the prodromal cohort with the unaffected Genetic Cohort. The Genetic Registry will allow exploratory assessments of genetic subjects with more advanced PD and of family members who are unable to participate in the Genetic Cohort.

## **15. Regulatory / Ethics**

### **15.1. Compliance Statement**

This study will be conducted in accordance with the Good Clinical Practice (GCP) and the International Conference on Harmonization (ICH) guidelines and any applicable national and local regulations.

All procedures not described in this protocol will be performed according to the study Operation Manuals unless otherwise stated. Laboratory tests/evaluations described in

this protocol will be conducted in accordance with quality laboratory standards as described in the central laboratory manual unless otherwise stated.

### **15.2. Informed Consent**

In accordance with relevant regulations, an informed consent agreement explaining the procedures and requirements of the study, together with any potential hazards/risks must be read by and/or explained to each subject. Each subject will sign such an informed consent form. The subject must be assured of the freedom to withdraw from participation in the study at any time. In addition, a Certificate of Confidentiality has been obtained to provide additional confidentiality protections for subjects at participating PPMI sites in the United States.

It is the Investigator's responsibility to make sure that the subject understands what she/he is agreeing to and that written informed consent is obtained before the subject is involved in any protocol-defined procedures including screening procedures. It is also the Investigator's responsibility to retain the original signed consent form and provide each subject with a copy of the signed consent form.

The CTCC must be given an opportunity to review the consent forms prior to site IRB submission and before it is used in the study.

Subjects will be encouraged to complete an Advance Directive for Clinical Research Participation, if willing, to document their wishes about participation in PPMI should they no longer be able to give informed consent. The advance directive permits a Substitute Decision Maker to be named to help make decisions for the subject concerning his/her participation in the PPMI study in the event the subject is no longer able to decide for him/herself (see Section 9.1).

